### Participant timeline

2.5

Pregnant women in the CS group are screened no earlier than 10 days before their scheduled CS. Participants in both groups complete 3 online or paper antenatal questionnaires approximately 2 weeks prior to their estimated due date. The mothers and their babies are followed for three months post birth. Figure 1 shows the flow of participants in both the vaginal and CS birth groups.

**Figure 1 F1:**
[figure not shown]
Flow of participants through the ECOBABe study.

### Sample size

2.6

We intend to randomize 30 healthy babies in the CS group on a 1:1 basis to intervention or placebo (15 per group). A power calculation indicated that 15 babies per CS group would be sufficient to detect a moderate effect size of 0.25 standard deviations for our primary outcome (power calculation for balanced one-way ANOVA test, 85% power, α = 0.05). In addition, we intend to recruit 15 babies born vaginally as a reference group.

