### Outcomes

2.4

Primary outcome:

Difference in the community structure of the gut microbiota between CS groups at 1 month of age.

Secondary outcomes:

Difference in the overall gut microbiota community between CS groups at 24 hours and 3 months of age.Similarity of CS seeded and placebo gut microbiota profiles to those born vaginally at 24 hours, 1 and 3 months of age.Degree of maternal vaginal bacterial strain transfer in CS-born babies at 24 hours, 1 and 3 months of age.BMI *z*-score at 1 and 3 months of age.Total body fat percentage from whole-body dual-energy absorptiometry (DXA) at 3 months of age.

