#### Microbial and statistical analyses

2.9.8

Metagenomic sequencing data will be processed with bioBakery workflows using docker images available at http://huttenhower.sph.harvard.edu/biobakery_workflows. Briefly, sequence data quality control, including removal of any human reads, will be conducted using KneadData. Taxonomic and functional profiles of the microbiota will be generated using MetaPhlAn v2.6^[52]^ and HUMAnN2^[53]^ respectively. Strain-level taxonomic profiling will be achieved by SNP haplotype based profiling using StrainPhlAn software.^[54]^ The resulting SNP haplotypes will be used to identify the proportion of shared and unrelated strains between mother-baby pairs, comparing these proportions across treatment groups.

Permutational multivariate analysis of variance (PERMANOVA) will be used to identify any significant differences in the overall microbial community structure between treatment groups. Additionally, Multivariate Association with Linear Models (MaAsLin2) will be used to identify any significant associations between specific microbial taxa and treatment groups. Both taxonomic and functional profiles will be compared. Microbiota stability across time points will be assessed using Bray Curtis dissimilarity. Microbial alpha diversity will be assessed using Shannon's diversity index and gene counts.

Treatment evaluation on clinical outcomes will be performed on the basis of intention to treat, using data collected from all randomized participants. Generalized linear regression models will be used to assess treatment effects, adjusting for sex. Model-adjusted estimates and the difference among the three groups will be calculated and tested. Planned subgroup analysis by sex may be conducted on secondary outcomes to evaluate the consistency of possible treatment effects in males and females. Analyses of non-microbiome data will be performed in SAS v9.4, SPSS v26, and/or Minitab v16. Statistical tests will be two-tailed and significance maintained at 5% level.

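### Sample size, effect size and power in section 2.6 do not fit together: 15 babies per arm gives 85% power only for a difference of about 1.1 SD, not 0.25 SD

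*Protocol article*

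**What the plan says.** Section 2.6 (Sample size) plans 30 caesarean-born babies randomised 1:1, 15 to each arm. It justifies this by stating that "15 babies per CS group would be sufficient to detect a moderate effect size of 0.25 standard deviations for our primary outcome". The method in brackets is "power calculation for balanced one-way ANOVA test, 85% power, α = 0.05". The vaginal-born babies come in the next sentence: "In addition, we intend to recruit 15 babies born vaginally as a reference group".

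Section 2.4 (Outcomes) defines the primary outcome as "Difference in the community structure of the gut microbiota between CS groups at 1 month of age", which is a two-group comparison.

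Section 2.9.8 (Microbial and statistical analyses) names the test: "Permutational multivariate analysis of variance (PERMANOVA) will be used to identify any significant differences in the overall microbial community structure between treatment groups". It also states: "Statistical tests will be two-tailed and significance maintained at 5% level".

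The article gives no other effect-size definition, variance or simulation in support of the power figure.

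**The concern.** Four inputs are printed: group size, effect size, test and alpha. Together they determine the power, and the printed value looks far too high. Fifteen per arm is small for a quarter of a standard deviation.

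The effect-size description is also odd. In ANOVA work 0.25 is the conventional medium value of Cohen's f, the standard deviation of the group means divided by the within-group standard deviation. With two equal groups, f = 0.25 is a difference of 0.5 SD, not 0.25 SD.

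This sentence is the only justification for the sample size on the primary outcome. Section 1.2 (Objectives) makes a larger study conditional on success here. A reader who trusts 85% power for a moderate effect could take a non-significant result as evidence that oral seeding does not work, when the study may have had little chance of showing a moderate effect.

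**Working it through.** **Inputs.** From section 2.6: n = 15 per group, balanced one-way ANOVA, alpha = 0.05, effect 0.25, stated power 85%. From section 2.4: k = 2 groups in the primary comparison. From section 2.9.8: two-tailed tests. Three groups of 15 are tried as a variant because section 2.6 also mentions the vaginal-born group.

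**Formula.** Power = P(F′ > F_crit), where F′ is noncentral F with k − 1 and k(n − 1) degrees of freedom and noncentrality λ = k·n·f². For two equal groups, a difference of d standard deviations gives f = d/2. Eta-squared converts by f² = η²/(1 − η²).

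Critical values: k = 2, df 1 and 28, F_crit = 4.20; k = 3, df 2 and 42, F_crit = 3.22.

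**Attempt to reproduce 85% as stated**

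| Reading of 0.25 | k | f² | λ | Power |
|---|---|---|---|---|
| difference of 0.25 SD (f = 0.125) | 2 | 0.015625 | 30 × 0.015625 = 0.469 | 10.1% |
| Cohen's f = 0.25 (0.5 SD) | 2 | 0.0625 | 30 × 0.0625 = 1.875 | 26.2% |
| f = 0.125 | 3 | 0.015625 | 45 × 0.015625 = 0.703 | 10.3% |
| Cohen's f = 0.25 | 3 | 0.0625 | 45 × 0.0625 = 2.813 | 28.5% |

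None is near 85%. A noncentral t calculation gives the same two-group values. One-sided testing, which section 2.9.8 excludes, would give only 16.4% at 0.25 SD and 37.9% at 0.5 SD.

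**Other metrics for 0.25**

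| Reading of 0.25 | k | f² | λ | Power |
|---|---|---|---|---|
| eta-squared | 2 | 0.25/0.75 = 0.333 | 30 × 0.333 = 10.0 | 86.3% |
| eta-squared | 3 | 0.333 | 45 × 0.333 = 15.0 | 92.7% |
| f-squared (f = 0.5) | 2 | 0.25 | 30 × 0.25 = 7.5 | 75.3% |
| f-squared (f = 0.5) | 3 | 0.25 | 45 × 0.25 = 11.25 | 83.4% |
| between-group variance, within-group variance 1 | 2 | – | (k − 1)·n × 0.25 = 3.75 | 46.4% |
| between-group variance, within-group variance 1 | 3 | – | (k − 1)·n × 0.25 = 7.5 | 65.4% |

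Treating all three visits as independent (45 observations per group) at f = 0.25 gives 65.0% for two groups and 73.2% for three.

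Two readings come close to 85%: eta-squared with two groups, and f-squared with three. On the two-arm scale the first is d = 2 × √0.333 ≈ 1.15 SD. An f of 0.5 on the same scale is 2 × 0.5 = 1.0 SD. Neither is moderate, and neither is 0.25 SD.

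**What 15 per arm can detect.** Solving for 85% power with k = 2 gives f ≈ 0.567 (λ = 30 × 0.567² ≈ 9.6), so d ≈ 1.13 SD. That is 1.13/0.25 ≈ 4.5 times the printed difference.

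**What the printed effects would need.** For 85% power with two arms: 73 per arm at f = 0.25 (72 gives 84.6%, 73 gives 85.1%), and 289 per arm at 0.25 SD.

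**The case against.** The strongest reply is that the power may be right and the label wrong. If 0.25 was a proportion of variance explained, two groups of 15 give 86.3%, which matches the two-arm comparison that sections 2.4 and 2.6 describe. That is also a natural scale here, because PERMANOVA reports R², the analogue of eta-squared. This part stands: the article does not show how 85% was derived, so it cannot be said which figure is the wrong one. It does not rescue the sentence, because an eta-squared of 0.25 is about 1.15 SD between two arms.

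Some stronger readings are tempting but unsupported:

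- *The study was sized on a three-group test that includes the non-randomised babies.* The 83.4% result might suggest this, but the two-group eta-squared reading is slightly closer to 85%, and section 2.6 introduces the vaginal-born group only after the power statement.
- *The primary test will miss a moderate effect about three times in four.* The 26% belongs to a univariate ANOVA. PERMANOVA power depends on distances and dispersion that the article does not give. The recomputation tests the printed calculation on its own terms only.
- *A null result will be misread.* The article calls the study an exploratory pilot and does not say how a null result will be interpreted. Misreading is possible, and no more than that can be claimed.

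Using ANOVA as a planning proxy is acceptable in a pilot. The pilot label does not correct a printed power figure.

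**Conclusion.** The point holds as an inconsistency: the sample size, effect size and power in section 2.6 cannot all be correct. Taken as written, power is about 10% (0.25 SD) or about 26% (Cohen's f = 0.25, that is 0.5 SD), against a stated 85%. If the 85% is kept, the effect is large: about 1.1 SD between two arms of 15, some 4.5 times the difference printed. On every reading the sentence overstates the study's sensitivity to moderate differences.

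It would go too far to say that the 85% itself is shown to be false, since the effect-size metric may be what is wrong.

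The figures assume a univariate, normally distributed summary with equal variances, 15 evaluable babies in each arm and a two-sided 5% level. They do not give the power of the PERMANOVA.

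**What to change.** Keep 30 randomised babies. Find out from the original calculation which metric the 0.25 was, then restate section 2.6 and remove the description of the effect as moderate and as 0.25 standard deviations. Possible wording:

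*With 15 babies per arm, a one-way ANOVA on a univariate summary has 85% power at a two-sided 5% level for a difference of about 1.1 SD (f about 0.57), and about 26% power for f = 0.25 (0.5 SD). This is an approximate guide to the planned PERMANOVA, whose power also depends on the between-sample distances. A non-significant result in this pilot could not rule out a moderate effect.*

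If the original input was eta-squared or f-squared, name it and give its equivalent in standard deviations.

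The cost is wording only: no extra babies and no change to design or analysis. The price is a less favourable printed figure.

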### Recruitment

2.7

Recruitment occurs in conjunction with midwives and obstetricians working throughout the Auckland region. In addition, targeted recruitment posts are placed on social media. Posters and study leaflets are also distributed across Auckland to places where pregnant women are likely to see them, for example, public and private obstetric clinics, midwifery clinics, and antenatal education classes. In addition, the research team attended a popular local pregnancy and early childhood fair, and spoke with interested pregnant women present.

Woman exposed to recruitment material may self-refer to the study by emailing, texting, or calling the research team, or through completion of a brief online form on the study webpage. With the permission of interested women, health professionals can also pass on their contact details to the study team. The research team is responsible for obtaining informed consent from all potential participants.

### Randomization, allocation, and blinding

2.8

Healthy CS-born babies are randomized in a 1:1 ratio to either treatment or placebo group, using computer-generated randomization. Mothers of randomized babies were blinded to group allocation; the researchers analyzing the primary outcome data, are blinded to baby group (active treatment, placebo, or vaginal-born reference group). For pragmatic reasons, it is not possible for the researcher administering the intervention to be blinded, as they are the only member of the research team present at a woman's CS. Participant un-blinding during the study is permissible in the case of any serious adverse events and upon recommendation by the study's independent data monitoring committee (DMC).

### Data collection and follow-up

2.9

#### Timing of assessments

2.9.1

Babies are assessed at three time-points over the course of the study: birth (24 hours), 1 month, and 3 months (Table 3). All mothers are assessed for eligibility in the antenatal period, with just postnatal maternal health issues recorded thereafter (Table 3). Mothers are reminded of their study visits via email or text message. Fuel vouchers and free parking are provided for all study visits, and taxis are booked for mothers who are unable to drive to appointments. Study visits are rescheduled if a mother indicates that she will be unable to attend at the booked time.

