### Study setting

2.1

The study is assessing the eligibility of pregnant women planning an elective CS or vaginal birth across the entire Auckland region of Aotearoa/New Zealand, where over 20,000 women gave birth in 2017.^[2]^ Maternal vaginal bacteria or placebo is administered to CS-born neonates in hospital theatres shortly after birth. Follow-up of most babies occurs at the Maurice and Agnes Paykel Clinical Research Unit, Liggins Institute, University of Auckland. Some one-month follow-ups occur at a facility closer to, or at, the participant's home (where onsite visit is not practicable).

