#### Baby anthropometry and body composition

2.9.6

At 1 and 3 months of age, all babies are weighed and measured while naked. They are weighed using an infant weighing scale. Crown-heel length is recorded three times using a neonatometer (Holtain Ltd., Crymych, UK) with gentle pressure applied to the legs to ensure the body is flat as possible. The median value of the three measurements will be used for analysis. Both the weighing scale and neonatometer are regularly calibrated. Head, abdominal, and chest circumferences are measured using disposable paper measuring tapes. At 3 months, baby body composition is assessed using DXA while wrapped in a blanket (Lunar Prodigy and Lunar iDXA, GE Medical Systems, Chicago, IL).

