#### Sample collection and processing

2.9.7

Baby stool samples are collected by the parents from fresh nappies within the first 24 hours of life, and again at 1 and 3 months of age. Approximately one gram of stool is collected using the scoop attached to the lid of a sterile specimen tube (Sarstedt, Nümbrecht, Germany, Catalogue #SARS80.623). The tubes are prefilled with 5 ml of DNA/RNA Shield^TM^ solution (Zymo Research, Irvine, California, US, Catalogue #R1100) enabling them to be kept stable at room temperature until transfer to the laboratory. Parents are asked to shake the tightly-closed tube to mix the stool with the solution immediately after collection. Parents record the date and time of sample collection on an accompanying collection card. Upon arrival at the laboratory, stool samples are split into 1 ml aliquots and stored at −80°C.

Maternal vaginal microbiota samples (2 ml of vaginal bacteria supernatant and the remaining half of the gauze swab) are collected from all mothers in the CS group just prior to their scheduled CS, and are kept on ice until transfer to −80°C.

Microbial DNA will be extracted using the ZymoBIOMICS^TM^ 96 MagBead DNA kit (Catalogue #D4308) according to the manufacturer's instructions. A blank DNA extraction control consisting of 1 ml of sterile water will be run in parallel for contamination testing. In addition, the ZymoBIOMICS^TM^ microbial community standard (Catalogue #D6300) will serve as an extraction bias control. DNA extracts will be quantified using the Qubit^TM^ dsDNA High Sensitivity Assay kit (Catalogue #Q32851) with a Qubit^TM^ 3.0 fluorometer. Whole metagenome shotgun sequencing will be performed by an independent accredited commercial provider.

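### Three-month DXA fat percentage is compared across three groups with sex as the only named covariate, although age at scan can vary and this outcome is not age-standardised

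*Protocol article*

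**What the plan says.** Under Outcomes (2.4), BMI enters as a *z*-score at 1 and 3 months, whereas total body fat from DXA enters as a percentage at 3 months.

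Under Timing of assessments (2.9.1), the schedule is nominal: "Babies are assessed at three time-points over the course of the study: birth (24 hours), 1 month, and 3 months (Table 3"). The same paragraph adds: "Study visits are rescheduled if a mother indicates that she will be unable to attend at the booked time". It also describes support for attendance: "Fuel vouchers and free parking are provided for all study visits, and taxis are booked for mothers who are unable to drive to appointments".

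Under Baby anthropometry and body composition (2.9.6): "At 3 months, baby body composition is assessed using DXA while wrapped in a blanket". Weight and length are taken at 1 and 3 months.

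Under Study setting (2.1), an alternative location is described for one visit only: "Some one-month follow-ups occur at a facility closer to, or at, the participant's home (where onsite visit is not practicable").

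Under Microbial and statistical analyses (2.9.8), the model for clinical outcomes is: "Generalized linear regression models will be used to assess treatment effects, adjusting for sex". The next sentence says that estimates and differences among all three groups will be calculated and tested. Age at measurement is not named.

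**The concern.** Fat percentage changes with age in early infancy, so two babies scanned at different ages are not directly comparable on the raw scale. A BMI *z*-score normally takes account of age; a raw fat percentage does not. If visits move, age at scan varies, and the stated model has no term to absorb that variation.

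The consequence differs by comparison. Between the two caesarean arms, allocation is random and mothers are blinded, so spread in scan age adds noise. Against the vaginal-born group there is neither randomisation nor blinding. Mothers recovering from surgery may attend at different times from mothers who gave birth vaginally. A systematic age gap would then appear as a group difference in fat percentage.

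A smaller practical point sits beside this. Only the DXA needs fixed equipment, yet weight, length and the last scheduled adverse-event questioning fall at the same 3-month visit, for which no off-site option is described.

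**Working it through.** The article gives no SD, age slope, visit window or attrition figure for fat percentage, so there is no stated figure to reproduce. The check shows how much age could matter under declared assumptions.

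**Inputs from the article**
- 15 babies per group, three groups (Sample size, 2.6)
- Model: three groups plus sex (2.9.8)

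**Assumed inputs, not in the article**
- Slope of fat percentage on age near 3 months: 2 to 4 points per month
- Between-baby SD at fixed age: 5 points
- SD of age at scan: 1 to 2 weeks
- 4.345 weeks per month

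**1. Precision between the caesarean arms**

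Added SD = slope × SD of age / 4.345. Variance ratio = 1 + (added SD)² / 5². SE inflation = √(variance ratio) − 1.

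| Slope (points/month) | SD of age (weeks) | Added SD (points) | Variance ratio | SE inflation |
|---|---|---|---|---|
| 2 | 1 | 0.46 | 1.008 | 0.4% |
| 2 | 2 | 0.92 | 1.034 | 1.7% |
| 4 | 1 | 0.92 | 1.034 | 1.7% |
| 4 | 2 | 1.84 | 1.136 | 6.6% |

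With a wider range (slope 1 to 4, SD 4 to 5 points, SD of age 0.5 to 2 weeks), the inflation stays under 3% whenever the SD of age is 1 week or less. It peaks at about 10% for slope 4, SD 4 and SD of age 2 weeks.

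**2. Bias between the caesarean arms**

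No systematic gap is expected. The chance difference in mean age has SE = SD of age × √(2/15), which is 0.37 weeks for an SD of 1 week and 0.73 weeks for an SD of 2 weeks.

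**3. Confounding against the vaginal-born group**

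Spurious difference = slope × age gap / 4.345. For an illustrative gap of 2 weeks:
- slope 2: 2 × 2 / 4.345 = 0.92 points, or 0.92 / 5 = 0.18 SD
- slope 4: 4 × 2 / 4.345 = 1.84 points, or 1.84 / 5 = 0.37 SD

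A 1-week gap halves these to 0.46 and 0.92 points. The SE of a difference between two groups of 15 is 5 × √(2/15) = 1.83 points, so a 2-week gap shifts the estimate by about 0.5 to 1.0 SE.

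**4. Cost of the extra term**

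With 45 babies, residual degrees of freedom go from 45 − 4 = 41 to 40. If age has no systematic gap between groups and is roughly normal, the expected increase in the variance of a group difference is 1 / (41 − 2) = 2.6%, or 1.3% on the SE. For the randomised comparison the term therefore about breaks even at 1.7% inflation, loses slightly at 0.4%, and gains clearly at 6.6%. The stronger reason for including it is the comparison in step 3.

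**The case against.** The strongest reply is that this is analysis detail. The article names sex but does not say that sex is the sole covariate, and a full analysis plan may add age. That has weight, and it is why the point is minor. Still, the article does state a model, and that model is applied to a comparison with a non-randomised group.

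A reader might infer more than the text supports:

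- **That 3-month outcomes are measured late or lost.** Nothing in the article reports lateness or attrition. Rescheduling is a retention measure, and transport support covers all visits. A moved visit may shift by hours or days, in either direction. Table 3, which is not reproduced in the text at hand, may give visit windows. Windows would limit the spread in age but would not put age into the model.
- **That stool profiles, including the primary outcome, are affected.** Parents collect stool from nappies at 1 and 3 months of age, into a solution that keeps it stable at room temperature. Timing is documented: "Parents record the date and time of sample collection on an accompanying collection card". A moved visit need not move the sample.
- **That safety information disappears with a missed visit.** Under Safety monitoring (2.11), mothers in the caesarean group are asked to report unexpected medical review or intervention promptly, outside the visits.

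The collection card covers stool only, and the article does not state that the scan date is recorded. The fix assumes that it is, or easily can be.

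**Conclusion.** The narrow point stands as a minor improvement. The stated model compares an outcome that is not age-standardised across three groups, one of them non-randomised, and does not name age at scan, although visits can be moved.

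For the randomised comparison, the effect is a small loss of precision: 0.4% to 6.6% on the SE under the main assumptions and at most about 10% under the wider ones, with no systematic bias expected. For the comparison with vaginal-born babies, confounding is possible. Its size depends on an age gap that the article neither reports nor rules out; 2 weeks would give 0.9 to 1.8 points. Every slope, SD and gap here is an assumption.

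Only fat percentage, one secondary outcome of a pilot study, is at issue. BMI *z*-score and the microbiota outcomes are not.

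**What to change.** In Microbial and statistical analyses (2.9.8), state that the fat-percentage model includes exact age at the DXA scan, from date of birth to date of scan, alongside sex. Confirm that the scan date is recorded. The cost is one degree of freedom. The term handles a linear age effect; it does not remove other differences between caesarean-born and vaginal-born babies.

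Optionally, in Study setting (2.1), extend the off-site arrangement already used at 1 month to the 3-month weight, length and adverse-event questioning where a unit visit is not practicable. With 15 per group, each baby kept is 1/15 = 6.7% of a group. The downside is some staff travel and no DXA for those babies.
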